1  
2  
3  
4  
5  
6  
7  
8  
9  
10  
11  
12  
13  
14  
15  
16  
17  
18  
19  
20  
21  
22  
23  
24  
25  
26  
27  
28  
29  
30

| Study design                 | Multi-center, open-label, randomized, controlled trial                                                                                                                                                                                                                                                                                                                                                                                                                                                                                                                                                                                                       |
| Primary objective            | To compare the efficacy and safety of Low-molecular-weight heparin (LMWH) plus insulin versus insulin alone in reducing the incidence of new-onset organ failure and/or mortality among patients with hypertriglyceridemia-associated acute pancreatitis (HTG-AP).                                                                                                                                                                                                                                                                                                                                                                                           |
| Study center(s)              | Up to 10 study centers                                                                                                                                                                                                                                                                                                                                                                                                                                                                                                                                                                                                                                       |
| Number of subjects (planned) | Approximately 540 randomized subjects                                                                                                                                                                                                                                                                                                                                                                                                                                                                                                                                                                                                                        |
| Subjects                     | 
Inclusion criteria
 
 
● Patients aged between 18 and 85 years;
 
● Acute pancreatitis diagnosed according to the 2012 revised Atlanta Classification;
 
● Time from acute pancreatitis onset to randomization within 48 hours;
 
● Serum triglyceride levels ranged from 11.3 mmol/L (equal to 1000 mg/dL) to 40 mmol/L (equal to 3550 mg/dL);
 
● Signed informed consent.
 
 
Exclusion criteria
 
 
● Biliary pancreatitis;
 
● Alcoholic pancreatitis;
 
● Pregnant or lactating females;
 
 |

|                              |                                                                                                                                                                                                                                                                                                                                                                                                                                                                                                                                                                                                                                                                                                                                                                                       |
|------------------------------|---------------------------------------------------------------------------------------------------------------------------------------------------------------------------------------------------------------------------------------------------------------------------------------------------------------------------------------------------------------------------------------------------------------------------------------------------------------------------------------------------------------------------------------------------------------------------------------------------------------------------------------------------------------------------------------------------------------------------------------------------------------------------------------|
|                              | 
 
● Disseminated intravascular coagulation or active bleeding;
 
● Allergy to heparin or insulin;
 
● Usage of any triglyceride-lowering treatments between symptoms onset and randomization, or blood purification treatment for acute renal failure;
 
● Cardiopulmonary resuscitation for cardiac arrest;
 
● Patients with irreversible organ failure or other critical manifestations who are expected to die within 24 hours;
 
● Advanced malignant tumors, immunodeficiency disorders, and a pre-existing chronic renal failure requiring regular hemodialysis;
 
● Conscious and behavioral abilities are partially or totally limited and unable to make decisions independently.
 
 |
| Treatments            | 
LMWH + insulin group
 
a 4000 IU of LMWH sodium injection (enoxaparin) will be injected subcutaneously once every 12 hours for three days.
 
Insulin adjusted on the glucose levels.
 
Insulin alone group
 
Insulin adjusted on the glucose levels.
                                                                                                                                                                                                                                                                                                                                                                                                                                                                                         |
| Duration of Treatment | Three days for LMWH.                                                                                                                                                                                                                                                                                                                                                                                                                                                                                                                                                                                                                                                                                                                                                                  |
| Follow-up             | All participants will be followed for a total of one month.                                                                                                                                                                                                                                                                                                                                                                                                                                                                                                                                                                                                                                                                                                                           |
| Informed consent      | Written informed consent will be obtained from all participants or their legal representatives.                                                                                                                                                                                                                                                                                                                                                                                                                                                                                                                                                                                                                                                                                       |
| Randomization         | Patients will be randomly assigned (1:1) to either LMWH plus insulin (LMWH + insulin group) or insulin alone (insulin group). Dynamic randomization will be used via a network-based center random software.                                                                                                                                                                                                                                                                                                                                                                                                                                                                                                                                                                          |

|                           |                                                                                                                                                                                                                                                                                                                                                                                                                                                                                                                                                                                                                                                                                                                                                                                                                                                                                       |
|---------------------------|---------------------------------------------------------------------------------------------------------------------------------------------------------------------------------------------------------------------------------------------------------------------------------------------------------------------------------------------------------------------------------------------------------------------------------------------------------------------------------------------------------------------------------------------------------------------------------------------------------------------------------------------------------------------------------------------------------------------------------------------------------------------------------------------------------------------------------------------------------------------------------------|
| Primary outcome    | A composite of new-onset organ failure and/or mortality within one month after randomization                                                                                                                                                                                                                                                                                                                                                                                                                                                                                                                                                                                                                                                                                                                                                                                          |
| Secondary outcomes | 1) New-onset organ failure including respiratory failure, renal failure, and circulatory failure; 2) Mortality; 3) The time to achieve the triglyceride goal of <5.65 mmol/L, which will be detected using a fully automated blood biochemistry analyser; 4) New-onset systematic inflammatory response syndrome; 5) Necrotizing pancreatitis; 6) Infected pancreatic necrosis; 7) Sepsis; 8) Pulmonary infection; 9) Vein thrombosis; 10 ) Pseudoaneurysm; 11) Sinistral portal hypertension; 12) Abdominal compartment syndrome; 13) Cerebral haemorrhage; 14) Demand for mechanical ventilation; 15) Renal replacement therapy; 16) Percutaneous drainage of ascites; 17) Drainage of pancreatic necrosis; 18) Debridement of pancreatic necrosis; 19) Vascular interventional therapy; 20) Duration of intensive care unit stay; 21) Length of hospital stay; 22) Hospital costs. |
| Safety outcomes    | new-onset bleeding, the rebound of serum triglyceride, and drug-related adverse events.                                                                                                                                                                                                                                                                                                                                                                                                                                                                                                                                                                                                                                                                                                                                                                                               |
| Study Timeline     | Recruitment period estimated in 36 months
Follow-up per patient: one month                                                                                                                                                                                                                                                                                                                                                                                                                                                                                                                                                                                                                                                                                                                                                                                                         |

32

33

34

35

36

37

38

39

40  
41  
42  
43  
44  
45  
46  
47  
48  
49  
50  
51  
52  
53  
54  
55  
56  
57  
58  
59  
60  
61  
62  
63  
64  
65  
66  
67  
68  
69

## 1 INTRODUCTION

Acute pancreatitis (AP) is a common gastrointestinal disease with multiple causes, including gallstones, alcohol, and hypertriglyceridemia (HTG). Basolateral secreted or leaked pancreatic lipase-mediated triglyceride (TG) lipolysis may play an important role in the initiation and exacerbation of hypertriglyceridemia-associated acute pancreatitis (HTG-AP). This lipolysis process leads to the accumulation of free fatty acids (FFAs), which can cause cytotoxic injury to the pancreas. Notably, increased serum TG levels have been linked to worse clinical outcomes, manifesting as persistent systemic inflammatory response syndrome (SIRS) and organ failure.

On that basis, there have been some treatment strategies introduced to reduce serum TG levels, including noninvasive measures such as fasting, insulin, and heparin, as well as invasive blood purification techniques. Despite these interventions, international guidelines for the early management of AP did not give any recommendations regarding specific TG-lowering therapy due to the lack of solid evidence. Nonetheless, in some clinical settings, insulin with or without heparin has emerged as a common therapeutic approach for the early management of HTG-AP. Heparin, including low-molecular-weight heparin (LMWH), stimulates the release of endothelial lipoprotein lipase (LPL) into circulation, while insulin activates LPL and reduces the activity of hormone-sensitive lipase, thereby increasing the clearance of chylomicrons from plasma.

Although heparin with insulin is commonly used for lowering-TG in the treatment of HTG-AP, the efficacy and safety of LMWH plus insulin in HTG-AP remains controversial. Our previous RCT showed that LMWH plus insulin not only rapidly decreased the TG levels within 48 hours, but also significantly decreased the incidence of respiratory failure in HTG-AP patients. Additionally, heparin might reduce pancreatic necrosis and improve organ function, by its anti-inflammation and antioxidative properties. However, the bleeding risk of low-molecular-weight heparin (LMWH) was significantly lower than that of unfractionated heparin, and it exerts

anti-inflammatory effects. A multicenter prospective study found that LMWH can reduce the incidence of complications, mortality and hospital stay in severe acute pancreatitis (SAP), and no haemorrhagic complications occurred. However, it was concerned that prolonged use of heparin might lead to a rebound of serum TG due to the LPL depletion, and increase the risk of pancreatic hemorrhage. However, our previous RCT showed that a short course of LMWH use for three days did not induce the rebound of TG or any serious bleeding event. In this multicenter RCT, we will compare the efficacy and safety of LMWH plus insulin versus insulin alone in reducing the incidence of new-onset organ failure and mortality in patients with HTG-AP.

## **2 TRIAL OBJECTIVES**

To compare the efficacy and safety of LMWH plus insulin versus insulin alone in reducing the incidence of new-onset organ failure and/or mortality in patients with HTG-AP.

## **3 OVERALL STUDY DESIGN**

### **3.1 Study design**

This is an investigator-initiated, multicenter, open-label, parallel, randomized, controlled trial.

### **3.2 Study population**

Adult patients admitted to any hospital of the participating hospitals with the primary diagnosis of AP meeting the inclusion criteria will be screened for inclusion into the study.

### **3.3 Inclusion criteria**

- Patients aged between 18 and 85 years;
- AP diagnosed according to the 2012 revised Atlanta Classification;
- Time from AP onset to randomisation within 48 hours;
- Serum TG levels ranged from 11.3 mmol/L (equal to 1000 mg/dL) to 40 mmol/L (equal to 3550 mg/dL);

- Signed informed consent.

### **3.4 Exclusion criteria**

- Biliary pancreatitis defined as the presence of dilated choledocholith, or meeting two of the following three laboratory abnormalities: (1) serum bilirubin concentration >1.9 mg/dL; (2) alanine aminotransferase (ALT) activity >100 U/L with ALT activity higher than the aspartate aminotransferase (AST) activity; and (3) alkaline phosphatase activity >195 U/L with  $\gamma$ -glutamyltransferase (GGT) activity >45 U/L;
- Alcoholic pancreatitis defined as a history of over 5 years of heavy alcohol consumption (>50 g per day);
- Pregnant or lactating females;
- Disseminated intravascular coagulation or active bleeding;
- Allergy to heparin or insulin;
- Usage of any TG-lowering treatments (including TG-lowering drugs, plasma exchange, or haemofiltration) between symptoms onset and randomisation, or blood purification treatment for acute renal failure;
- Cardiopulmonary resuscitation for cardiac arrest;
- Patients with irreversible organ failure or other critical manifestations who are expected to die within 24 hours, including patients with severe ARDS requiring extracorporeal life support ( $\text{FiO}_2/\text{PO}_2 < 60$  if  $\text{PEEP} > 10$  cm  $\text{H}_2\text{O}$  and  $\text{FiO}_2 = 100\%$ ), severe systemic circulatory failure (a systolic blood pressure <90 mmHg and serum pH values <7.0 given full-fluid resuscitation and norepinephrine usage at a dose of 25  $\mu\text{g}/\text{min}$ ), or severe coma without sedation drugs with a Glasgow score equal to three points;
- Advanced malignant tumours, immunodeficiency disorders, and a pre-existing chronic renal failure requiring regular haemodialysis;
- Conscious and behavioural abilities are partially or totally limited and unable to make decisions independently.

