### **4.3 Intervention Group (LMWH + insulin group)**

In the LMWH + insulin group, a 4000 IU of LMWH sodium injection (enoxaparin) will be injected subcutaneously once every 12 hours for three days. Continuous usage of LMWH at prophylactic dosages will be considered for patients assessed to be at high-highest risk of venous thromboembolism and low bleeding risk, which was on chief physician's discretion.

For those with a glucose level > 11.1 mmol/L, patients will receive micropumps of insulin at 2 to 6 U/h, monitor blood glucose closely, to maintain the serum glucose levels between 7.8 and 10 mmol/L. When the glucose levels fall below 7.8 mmol/L, 6 U of insulin will be added to 500 mL of 5% glucose for intravenous infusion until the TG levels decrease to less than 5.65 mmol/L (500 mg/dL) or for a maximum duration of 5 days after randomization, whichever occurs first. For those with a glucose level ≤11.1 mmol/L, patients will receive 6 U of insulin with 500 mL of 5% glucose for intravenous, twice a day for 5 days, if hypoglycemia occurs, 5% dextrose change to 10% dextrose.

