### **4.5 Drug Withdrawal Standard**

When TG levels reach less than 500 mg/dL or at 5 days after enrollment, insulin will

be stopped and oral lipid-lowering drugs will be administered in the above two groups. If the blood glucose level is still greater than 11.1 mmol/L, insulin will be maintained to control the blood sugar. While LMWH administration was limited to 3 days (irrespective of triglyceride levels) in the LMWH + Insulin Group. However, LMWH (4000 IU every 12 hours for 7-10 days) was administered as venous thromboembolism (VTE) prophylaxis in high-risk patients (Padua score  $\geq 4$ ), and with low bleeding risk in both groups.

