## **10 Discussion**

This study was the first randomized trial comparing LMWH plus insulin versus insulin alone in patients with HTG-AP admitted within 48 hours. The initial version of the study protocol was a multicenter, prospective, single-blind, randomized controlled trial, which was published in *Pancreas*. However, before the study was initiated, the protocol was revised after all the research centers discussed it: firstly, the ethical committees at some centers reviewed that LMWH was also needed for patients entering the insulin group who were at very high risk of thrombosis. In addition, patients at 48 hours of onset endured pain, and the additional subcutaneous injection of placebo (saline) in the control group added to patient suffering, so changing from single-blind to open-label was recommended due to poor feasibility; secondly, statisticians recommended revising the sample size from 476 to 540 cases based on the calculations of a superiority trial; thirdly, experts recognized that acute renal failure increases the risk of hemorrhage with LMWH, and that these patients need to undergo blood purification, which affects TG levels, so they were excluded. Finally, we retracted the original protocol after discussion, and the revised protocol was approved by the Ethics Committees and updated in the Clinical Trial Registry(<https://www.chictr.org.cn/showproj.html?proj=28529>).

The reason for placing an upper limit on TG levels will be based on the ethics committee's advise; prior to the initiation of this study, several research centers routinely placed patients with TG >3550 mg/dL on plasma exchange in clinical practice, as it has been reported that hemodialysis of patients with extremely high levels of serum TG shortens the length of hospital stay.

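### Non-trial LMWH follows two inconsistent rules (4.3 and 4.5), neither tied to an assessment before open-label allocation; separately, 3.4 does not exclude clear high bleeding risk such as a recent major bleed

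*Protocol*

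**What the plan says.** **Entry.** Protocol 3.4 excludes "Disseminated intravascular coagulation or active bleeding". It also excludes patients on blood purification for acute renal failure ("or blood purification treatment for acute renal failure") and those with chronic renal failure on regular haemodialysis. It has no other criterion aimed at bleeding risk.

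**Randomised treatment.** Under 4.3, in the LMWH arm, "a 4000 IU of LMWH sodium injection (enoxaparin) will be injected subcutaneously once every 12 hours for three days".

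**Non-trial LMWH, first rule.** Section 4.3, which covers the LMWH arm, has continued use at prophylactic doses considered for "patients assessed to be at high-highest risk of venous thromboembolism and low bleeding risk", "which was on chief physician's discretion".

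**Non-trial LMWH, second rule.** Section 4.5 states that "LMWH (4000 IU every 12 hours for 7-10 days) was administered as venous thromboembolism (VTE) prophylaxis in high-risk patients", defined there by a Padua score of 4 or more, "and with low bleeding risk in both groups".

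**Context.** Section 4.2 makes the trial open-label for participants and investigators. Section 5.3 counts new abdominal or gastrointestinal bleeding over the first two weeks. The schedule in Figure 2 shows baseline variables at admission and Day 0 without listing them.

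**The concern.** Two separate matters meet here.

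The first is control of a co-treatment that is the study drug itself. A patient in the LMWH arm falls under both 4.3 and 4.5, which set different thresholds and different ways of deciding. A patient in the insulin arm falls under 4.5 alone. If risk is judged after allocation by someone who knows the arm, use of non-trial LMWH may come to depend on the arm. The two-week bleeding comparison would then no longer reflect the randomised course alone.

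The second is patient safety at entry. Both non-trial rules require low bleeding risk, so the protocol treats bleeding risk as relevant to LMWH. Yet a patient who bled seriously a short time ago but is not bleeding now, or who takes a non-heparin anticoagulant at therapeutic dose, meets no exclusion on that ground and can be allocated to LMWH. The safety endpoints, the six-monthly IDMC review and serious adverse event reporting all operate after the first dose.

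**Working it through.** **1. The two rules side by side**

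| | 4.3 | 4.5 |
|---|---|---|
| Arm | LMWH + insulin | Both |
| VTE threshold | Verbal grade, no score | Padua score of 4 or more |
| Bleeding condition | Low risk, undefined | Low risk, undefined |
| Decision | Considered, at discretion | Given when criteria are met |
| Dose | Prophylactic, no IU | 4000 IU every 12 hours |
| Duration | Not stated | 7-10 days |
| Time of assessment | Not stated | Not stated |

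The rules share the bleeding condition and the missing assessment time. They differ on threshold, decision and detail. They also cite different sources: a paper on thrombosis risk assessment for 4.3, and a haematology society guideline on VTE prophylaxis for 4.5.

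**2. Exposure**

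Dose = 4000 IU × 2 per day × days.

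- Randomised course: 4000 × 2 × 3 = 24,000 IU.
- A 4.5 course: 4000 × 2 × 7 = 56,000 IU, up to 4000 × 2 × 10 = 80,000 IU.

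Section 4.5 does not say whether, in the LMWH arm, the 7-10 days include the three trial days.

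- If they are additional, an LMWH-arm patient receives 24,000 + 56,000 = 80,000 IU, up to 24,000 + 80,000 = 104,000 IU in all. An insulin-arm patient on a course of the same length receives 24,000 IU less, which is the planned difference.
- If they are a total, the extra in the LMWH arm is 4-7 days, or 32,000-56,000 IU. Both patients then receive 56,000-80,000 IU, and the difference between them is 0.

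So among patients who qualify under 4.5 the planned contrast is either kept or removed, depending on a reading that the text leaves open. This is so even if non-trial use is equal in the two arms.

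**3. Overlap with the bleeding window**

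The start day s of non-trial LMWH is not given, so it is left free. For a course of L days, the days inside the 14-day window are min(L, 14 − s).

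- A 7-day course lies wholly inside if s ≤ 7, and a 10-day course if s ≤ 4.
- Added straight after the trial course (s = 3), a 10-day course ends on day 13, still inside.
- At s = 7, 7 days fall inside and a 10-day course runs 3 days past.
- At s = 10, 4 days fall inside.

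Any start before day 14 gives some overlap.

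**4. Entry criteria against the example patients**

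A recent major bleed that has stopped is not active bleeding and meets no other item in 3.4. Therapeutic anticoagulation is not listed. Heparin given after symptom onset may already be barred, because 3.4 excludes prior TG-lowering treatment and section 1 counts heparin as one. The anticoagulant example therefore applies mainly to non-heparin drugs.

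**5. What cannot be computed**

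The protocol gives no share of patients with a Padua score of 4 or more, none with raised bleeding risk, and no bleeding rate by exposure. Neither the number affected nor the effect on bleeding follows from it.

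**The case against.** The strongest reply has four parts.

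- **Bleeding was considered.** Section 3.4 has bleeding exclusions, section 10 gives haemorrhage risk with LMWH as a reason for the renal exclusion, and section 1 reports no serious bleeding with a three-day course in the group's earlier trial. This stands as evidence of attention to the risk. It does not supply a check before the first dose for the two kinds of patient named above.
- **A longer course may deserve a stricter condition.** Section 4.5 governs 7-10 days and the trial course lasts three. This stands. It is why the entry point is a gap: a reader might infer that 3.4 contradicts 4.5, and it does not.
- **The rules can be read together.** Continuation in 4.3 can only concern the arm already on LMWH, and 4.5 could be taken as the specific rule that fills in the dose, score and duration. This narrows the conflict. It does not settle whether an LMWH-arm patient with a Padua score of 4 or more receives the course by rule or only if the chief physician chooses.
- **Assessment after allocation is not a fault in itself.** VTE risk changes during the illness, and the case report form, not at hand, may record it at baseline. Both points are fair. The protocol still does not require a record before allocation, and that record is what would separate a clinical change from a choice made in knowledge of the arm.

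**Conclusion.** The point holds as a recommended change, with medium confidence. Sections 4.3 and 4.5 are inconsistent for the LMWH arm, the risk assessment behind both is undefined on bleeding and untimed relative to open-label allocation, and 3.4 leaves a narrow safety gap. The exposure at issue is 56,000-80,000 IU per 4.5 course against 24,000 IU randomised, mostly or wholly inside the bleeding window if started in the first week. The effect on bleeding and the number of patients affected are unknown.

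Three stronger readings are not supported:

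- A reader might infer that the arms will receive non-trial LMWH differently. The open-label design and the one-arm discretion make that possible; nothing in the protocol shows it.
- A reader might take the section 10 wording, "LMWH was also needed for patients entering the insulin group who were at very high risk of thrombosis", as a third threshold. It recounts why the earlier single-blind protocol was revised and is not a dosing rule.
- A reader might turn the doses above into a size of bias by assuming a difference in use between arms. Any such difference would be invented, the result would depend on whether 7-10 days is a total, and a shift in dose is not an effect on bleeding.

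**What to change.** 1. Before randomisation, record the Padua score and the bleeding risk in every patient, the latter by a definition stated in the protocol.
2. Delete the discretion in 4.3 and apply the 4.5 rule (Padua score of 4 or more and low bleeding risk) from that record in both arms. State whether the 7-10 days include the three trial days. Allow later clinical changes, with date and reason, and report non-trial LMWH by arm.
3. Add to 3.4 a narrow exclusion for recent major bleeding or current therapeutic anticoagulation. It should not extend to everyone who falls short of low bleeding risk.

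The cost is amendment wording and slightly more baseline work, since 4.5 already needs the assessment in both groups. A few screened patients would be lost to the new exclusion, number unknown. Documented later changes still leave some room for decisions made in knowledge of the arm, but make them visible. No stated sample-size figure changes.
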